## Abstract

**Background:**

Total knee arthroplasty (TKA) is an important management strategy for patients with knee osteoarthritis (OA) refractory to conservative management. Postoperative range of motion (ROM) exercise is important to recover patients’ activities of daily living. Continuous passive motion (CPM) is a machine that provides passive ROM exercises of the knee joint in a pre-defined arc of motion. The short- and long-term effects of CPM exercise are controversial. We hypothesized that the inconsistent results of the CPM exercise are due to poor fitting of CPM machines and measurement errors. This study aims to present a protocol for investigating a new type of CPM machine that could be applied in a sitting position in comparison with the conventional type of CPM machine for patients with unilateral TKAs.

**Methods:**

This study presents the protocol of a prospective, multicenter, single-blinded, three-armed randomized controlled trial (RCT). One hundred and twenty-six patients receiving unilateral TKAs will be recruited at the physical medicine and rehabilitation clinics of two urban tertiary medical hospitals. The patients were randomly divided into three groups with a 1:1:1 allocation. The intervention group will receive two weeks of post-operative rehabilitation using a new type of CPM machine. The control group will receive 2 weeks of post-operative rehabilitation using conventional CPM machines. The third group will receive post-operative rehabilitation with both types of CPM machines. The primary outcome will be the change in the passive ROM of the affected knee joint from baseline to 2 weeks after baseline assessment. The secondary outcomes will be pain and functional measurements, and will include patient-reported outcomes and performance tests surveyed at multiple time points up to 3 months after TKA.

**Discussion:**

This is the first RCT to investigate the effect of a new type of CPM machine. The results of this RCT will determine whether the position of the patients during CPM exercise is important in post-operative rehabilitation protocols after TKAs and will provide evidence for the development of proper rehabilitation guidelines after TKAs.

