Many researchers and clinicians do not believe that these slight statistical differences in ROM lead to meaningful clinical outcomes. Moreover, the long-term efficacy of CPM after TKAs has been questioned by many researchers. Some studies showing the superiority of CPM over physical therapy alone applied the regimens with a larger arc of motion [10, 11]. Bible et al. found discrepancies between the pre-defined arc of motion in CPM and the actual arc of knee motion [12]; this can be a potential reason for the controversy in the results of studies using a CPM machine. Therefore, proper fitting and setting of the true knee motion manipulated by CPM can be key factors in post-operative rehabilitation using CPM machines. Moreover, Bible et al. discovered that increasing the angle of inclination of the bed from 30° to 60° enhances the accuracy of the CPM protocol [12].

Therefore, changing the inclination of the bed could be a useful modification of the CPM protocols to enhance effective postoperative rehabilitation. Conventional models of CPM machines are applied in the supine position, and additional bed modifications are required to change the bed tilt angle. However, a CPM machine (Resilion K20P, HEXAR Humancare, Korea, Fig. 1) that can be used in a sitting position has been developed and is currently being applied to patients [13]. However, to the best of our knowledge, there are no reports comparing the effects of CPM between lying and sitting positions in patients receiving TKRs.

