**Fig. 1 Fig1:**
[figure not shown]
A new type of CPM machine (Resilion K20P®, HEXAR humancare, Korea) will be used in this randomized trial

We hypothesized that the efficacy of CPM machines in patients receiving TKRs differed according to the position of the patients and that CPM machines applied in the sitting position of patients would be more effective than conventional methods of CPM treatment. Therefore, the purpose of this study was to compare the effect of conventional CPM and CPM treatments applied in the sitting position in patients receiving TKAs and to establish a more suitable rehabilitation strategy using a CPM machine.

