#### Randomization, allocation, and blinding

Orthopedic surgeons perform an initial screening of all patients who visit the department of orthopedic surgery due to degenerative knee OA. If the patients fulfill the eligibility criteria, they are referred to the principal study coordinator. The principal study coordinator performs the final eligibility assessment and asks for informed consent to enroll in this study. After their consent is obtained, participants are randomly assigned to each group in a 1:1:1 ratio to the conventional type, mixed type, and sitting type CPM groups. Block randomization will be used on groups of 12 to balance relocation into the intervention groups. After the initial allocation, the mixed CPM groups will be re-allocated into two groups. Mixed groups will receive combined interventions with two types of CPM machines and consist of two subgroups. One of the subgroups will receive intervention using the conventional type of CPM, followed by the sitting type of CPM, and the other subgroup will recieve intervention in the opposite order. This trial will be blinded to the assessor; after randomization, the allocation of participants will be confidentially managed by the principal study coordinator. All assessments will be conducted by a single trained physiotherapist in each hospital who is experienced in post-operative rehabilitation treatment and will be blinded to group allocation. Due to the nature of the study, participants will not be blinded and will be instructed not to communicate with any other researcher or physiotherapists about their interventions to minimize potential bias. If participants would like to discuss their rehabilitation program during the intervention, they will be able to do so with the unlabeled study coordinator.

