#### Intervention protocol

All participants will undergo primary unilateral TKA at the Department of Orthopedic Surgery. The day before the surgery, all participants will be admitted to the ward. On the day of admission, basal demographics and outcomes will be collected by the assessor. All participants will be instructed on the interventions and post-operative exercise programs. The participants will start the intervention program on postoperative day 3, the day after the removal of the surgical site drainage system. Two CPM systems (sitting type and conventional type) will be applied to the allocated group of participants (Fig. 3). The pre-defined arc of the angles in the CPM machines will be determined according to the ROM of the knee joint measured before each intervention. The assessor will measure the maximal passive ROM of the knee joint by using a goniometer. The ROM measurements will be taken in all three positions: supine, sitting, and prone. The setting arc of the angles of the CPM machines will be determined by adding 10° to the highest measured values in the ROM in the three positions. On the first day, interventions will be applied twice daily for 30 min. From the second day to the end of the intervention, CPM machines will be applied twice a day for 1 h in each session, for a total of 2 h per day. All participants were mobilized as tolerated using a walker or crutches. Conventional CPM will be performed using the RCF1121® (CARETECH, Gumi-si, Gyeongsangbuk-do, Korea). The CPM machines used in the sitting position will be Resilion K20P® (HEXAR Humancare, Ansan-si, Gyeonggi-do, Korea). Each group of participants will receive 10 sessions of intervention using the allocated CPM machines. The group of participants planned using both types of CPM machines will consist of two sub-groups, one of which will receive intervention for 5 consecutive days using the conventional type of CPM, followed by 5 days of intervention using the sitting type of CPM, and the other sub-group will receive intervention in the opposite order.

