The authors hypothesized that these inconsistent results were due to the improper fitting of CPM machines with patients and measurement error of ROM between studies. Good to excellent inter-tester reliability and intra-tester reliability have been reported for measuring the ROM in the native knee using a simple goniometer [34, 35]. However, measuring the knee joint ROM in patients after TKA shows that 22% of the goniometer measurements had more than 5° differences from the true degree of knee flexion [36]. Therefore, we decided to apply more objective tools to measure the ROMs using a digital inclinometer and a hand-held dynamometer. Therefore, this randomized trial will be conducted using more objective measurement tools and exact prescribed pre-defined arc ranges than previous trials using CPM machines.

In conclusion, the randomized trial will provide evidence of using a new type of CPM machine applied in the sitting position to incorporate the use of CPM into post-operative rehabilitation guidelines in patients receiving TKAs.

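### The trial claims to test patient position, but position and device change together in every arm, so only the device-plus-position package can be compared.

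*Protocol article*

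**What the plan says.** Two statements in the protocol article attribute the effect under study to the patient's position:

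- Abstract, Discussion: the results "will determine whether the position of the patients during CPM exercise is important".
- Background, hypothesis paragraph: the authors hypothesised that "the efficacy of CPM machines in patients receiving TKRs differed according to the position of the patients".

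The design is described in three places:

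- Randomization, allocation, and blinding: "participants are randomly assigned to each group in a 1:1:1 ratio to the conventional type, mixed type, and sitting type CPM groups". The mixed group is then divided into two order subgroups.
- Intervention protocol: "Conventional CPM will be performed using the RCF1121", and "The CPM machines used in the sitting position will be Resilion K20P". These are devices from two manufacturers. The mixed group has 5 days on one type and then 5 days on the other, in either order.
- Background: "Conventional models of CPM machines are applied in the supine position, and additional bed modifications are required to change the bed tilt angle". The authors then describe the evidence gap as one between lying and sitting.

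The legend of Fig. 3 adds that each device is set up as its manufacturer instructs. No arm, subgroup or period is described in which the conventional device is used seated or the new device supine.

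**The concern.** A trial can attribute a difference to position only if position varies while the device stays fixed, or if the two are crossed somewhere. Here they always move together. A better result with sitting CPM could come from sitting, from the Resilion K20P itself, or from both. A null result could mean that neither matters, or that the two effects offset each other.

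The rival explanation is one the authors raise themselves. The abstract's Background and the main Discussion name poor fit between CPM machine and patient as a suspected reason for inconsistent earlier results, and two devices from different makers may fit differently. If the two position statements stand, a finding about a pair of products could be reported and cited as a finding about posture.

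**Working it through.** The plan gives no figure to reproduce here. The question is what the design can identify.

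**Step 1. Combinations of device and position that occur**

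| | Conventional mode (supine, inferred) | Sitting |
|---|---|---|
| RCF1121 | conventional arm; one 5-day period of each mixed subgroup | none |
| Resilion K20P | none | sitting arm; the other 5-day period of each mixed subgroup |

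Two of the four cells are empty, and the filled cells lie on the diagonal.

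**Step 2. Arm means**

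Let μ be the mean under conventional CPM, δ the effect of changing device and π the effect of changing position. Code each arm by its share of sessions on the new device and its share of sessions seated:

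- conventional: (1, 0, 0), mean μ
- sitting: (1, 1, 1), mean μ + δ + π
- mixed: (1, 0.5, 0.5), mean μ + 0.5(δ + π)

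The three contrasts are then:

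- sitting − conventional = δ + π
- mixed − conventional = 0.5(δ + π)
- sitting − mixed = 0.5(δ + π)

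Every contrast is a multiple of the sum δ + π, and none contains π without δ.

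**Step 3. Rank**

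The device and position columns are identical, (0, 1, 0.5). The matrix has 3 columns but its computed rank is 2. Adding one hypothetical crossed cell, the new device used in the conventional position (1, 1, 0), raises the rank to 3. This shows that the missing crossed cell is the cause. It is a diagnostic and not a proposal for a new arm.

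**Step 4. Order subgroups**

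Splitting the mixed arm by order does not help. Within each period the pair (device, position) is either (0, 0) or (1, 1), so the columns still coincide. This holds whatever is assumed about additivity or carry-over, because the two off-diagonal cells are never observed.

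**Step 5. Illustration with the pilot means**

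Sample size calculation gives pilot post-treatment passive ROM means of 105.2 (conventional) and 100.0 (sitting). The difference is 100.0 − 105.2 = −5.2°. Each of these splits fits it equally well:

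- π = −5.2, δ = 0
- π = 0, δ = −5.2
- π = +5.2, δ = −10.4, since 5.2 − 10.4 = −5.2

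With 6 pilot patients in each of these two groups, this says nothing about the true difference. It shows only that the data cannot choose between the splits, and more patients would not change that.

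**The case against.** The strongest reply is that the article mostly describes what the design delivers. The abstract gives the aim as comparing a new machine usable in a sitting position with the conventional type. The abstract's Methods defines the arms by machine, the overview of research design speaks of two types of CPM, and the sample size section states the primary hypothesis as a difference between groups without mentioning position. The sentence just before the one quoted from the abstract also speaks of the new machine. All of this stands, and it limits the point to one sentence in the abstract and one clause in the Background.

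It can also be said that the arc-setting rule, session length and frequency are stated once, without distinction between machines, so some routes by which the devices could differ are set alike. That is fair. It does not equalise fit or the motion actually delivered at a given setting, so it reduces the confounding in part and does not remove it.

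Four stronger readings are tempting, and the documents do not support them:

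- **That the gap between set and actual knee arc is a property of the machine.** The Background calls this gap a potential reason for inconsistent results and reports that greater bed inclination improved accuracy. The gap therefore depends at least partly on position, which is the authors' rationale for sitting.
- **That measuring achieved against set arc would separate the effects.** Any such measurement would itself be made on one device in one position, so it inherits the same confounding.
- **That these two devices could simply have been crossed.** The Background says of conventional models that "additional bed modifications are required to change the bed tilt angle". It does not say that the RCF1121 can be used seated or the Resilion K20P supine.
- **That the closing aim "to incorporate the use of CPM into post-operative rehabilitation guidelines" overreaches in the same way.** The full sentence names the new machine applied in the sitting position, which is the package. Whether CPM should be used at all is a separate question about the lack of a group without CPM, and the sentence does not claim to test it.

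**Conclusion.** The point holds for the abstract's conclusion and the Background hypothesis. Position and device are completely confounded across all three arms and both periods of the mixed arm. Only their combined effect can be estimated, and no sample size or analysis plan changes that.

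A reader might infer that the trial is therefore invalid. It is not: the randomised comparison of Resilion K20P used sitting against RCF1121 used conventionally is sound in this respect, and it is what most of the article describes. Only the attribution to position fails.

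The conclusion rests on one inference. Supine use of the RCF1121 is taken from the general statement about conventional models in the Background; the Intervention protocol does not repeat it, and Fig. 3 is not available. If the RCF1121 were also used seated for some patients, the confounding would be incomplete, but the article describes no such use. The possibility of opposing device and position effects is logical only, as the documents give no evidence for it.

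**What to change.** Change two places in the protocol article, and carry the same wording into the results paper:

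1. **Abstract, Discussion.** Replace the claim about determining the importance of position with a statement that the trial compares two device-plus-position packages: Resilion K20P used sitting and RCF1121 used conventionally.
2. **Background, hypothesis paragraph.** State the hypothesis as a difference in efficacy between these two packages. Add one sentence saying that device and position are not crossed, so neither a difference nor its absence can be attributed to position alone.

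The remaining descriptions of the comparison, including those in the main Discussion, can stay. Arms, randomisation, outcomes, sample size and analysis are unaffected. Trial status reports 68 patients recruited and recruitment still open, so the claim can be narrowed before results are known. The cost is a few sentences and a narrower claim.

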**Trial registration:**

Clinical Research Information Service of Republic of Korea, KCT0005520, Registered on 21 October 2020, https://cris.nih.go.kr/cris/search/detailSearch.do/21750

**Supplementary Information:**

The online version contains supplementary material available at 10.1186/s12891-022-05507-2.

## Background

Knee osteoarthritis (OA) is a joint disease characterized by the failed repair of joint damage caused by external stress [1]. Symptoms and signs of knee OA include pain, stiffness, and reduced range of motion (ROM), resulting in discomfort and reduced physical activity in older adults.

Several guidelines suggest non-pharmacological and pharmacological treatments and emphasize the importance of maintaining physical fitness and avoiding sedentary lifestyles for patients with OA [2–4]. In cases of refractory knee OA, surgical treatment can be a useful clinical management tool. Among surgical procedures, total knee arthroplasty (TKA) is one of the most successful and has resulted in a substantial increase in quality-of-life gain in patients with refractory arthritis [5].

Continuous passive motion (CPM) machines provide passive ROM exercises of the knee joint in a pre-defined arc of motion. CPM can be used in the early rehabilitation of patients after TKAs and has been suggested to have advantages in regaining ROM of the knee joint in several reports in the 1980s [6, 7]. Recent systematic reviews show controversy in routine use of CPM and its advantages. A Cochrane review on CPM after TKAs was published in 2014. In this review, CPM increased active knee flexion ROM by only 2° compared to the control groups and did not have clinically important short-term effects on pain. CPM reduced the risk of manipulation and adverse events, although the quality of evidence was very low [8]. Yang et al. reported a systematic review on use of CPM after TKAs in 2021, which demonstrated a slight difference in active knee extension at 1 week (mean difference = 3.00°, *P* = 0.019), passive knee extension at 1 week (mean difference = 3.00°, *P* = 0.031), and at 3 months (mean difference = 3.00° *P* = 0.019) compared with the control groups [9].

Many researchers and clinicians do not believe that these slight statistical differences in ROM lead to meaningful clinical outcomes. Moreover, the long-term efficacy of CPM after TKAs has been questioned by many researchers. Some studies showing the superiority of CPM over physical therapy alone applied the regimens with a larger arc of motion [10, 11]. Bible et al. found discrepancies between the pre-defined arc of motion in CPM and the actual arc of knee motion [12]; this can be a potential reason for the controversy in the results of studies using a CPM machine. Therefore, proper fitting and setting of the true knee motion manipulated by CPM can be key factors in post-operative rehabilitation using CPM machines. Moreover, Bible et al. discovered that increasing the angle of inclination of the bed from 30° to 60° enhances the accuracy of the CPM protocol [12].

Therefore, changing the inclination of the bed could be a useful modification of the CPM protocols to enhance effective postoperative rehabilitation. Conventional models of CPM machines are applied in the supine position, and additional bed modifications are required to change the bed tilt angle. However, a CPM machine (Resilion K20P, HEXAR Humancare, Korea, Fig. 1) that can be used in a sitting position has been developed and is currently being applied to patients [13]. However, to the best of our knowledge, there are no reports comparing the effects of CPM between lying and sitting positions in patients receiving TKRs.

**Fig. 1 Fig1:**
[figure not shown]
A new type of CPM machine (Resilion K20P®, HEXAR humancare, Korea) will be used in this randomized trial

We hypothesized that the efficacy of CPM machines in patients receiving TKRs differed according to the position of the patients and that CPM machines applied in the sitting position of patients would be more effective than conventional methods of CPM treatment. Therefore, the purpose of this study was to compare the effect of conventional CPM and CPM treatments applied in the sitting position in patients receiving TKAs and to establish a more suitable rehabilitation strategy using a CPM machine.

## Methods/design

### Overview of research design

This is a randomized, controlled, three-arm, assessor-blinded trial comparing two types of CPM in acute rehabilitation after unilateral TKA in patients with degenerative knee OA in two tertiary urban medical hospitals. We followed the SPIRIT statement [14] to report the protocol and the SPIRIT Checklist are attached as Additional file 1. Fig. 2 provides an overview of the study’s conduct, review, description, and interpretation.

**Fig. 2 Fig2:**
[figure not shown]
The trial flow diagram

Written informed consent will be obtained from all the patients. The ethical validity of the trial was assessed and approved by the Institutional Review Boards of Chungnam National University Hospital (CNUH-2020-07-028) and the Catholic University of Korea, Daejeon St. Mary Hospital (DC20DNDI0089). This clinical trial was registered with the Clinical Research Information Service (KCT0005520).

### Participants

#### Eligibility criteria

Eligible participants will be patients scheduled to undergo primary unilateral TKA owing to degenerative changes. Other inclusion criteria will be as follows: 1) age 19 years or older and 2) agreement to participate in this randomized trial.

#### Exclusion criteria

The exclusion criteria will be as follows: 1) age under 60 years old or over 90 years old; 2) cause of arthritis other than degenerative changes (infection, trauma, and inflammatory joint disease); 3) history of previous hip, knee, or ankle orthopedic surgery; 4) history of previous lumbar surgery within 3 months of the study; 5) serious nervous system, cardiovascular diseases, or osteoporosis; 6) coagulation disorders; 7) patients with obesity whose body mass index is more than 35 kg/m^2^, 8) inability to understand the study protocols due to cognitive deficits or language problems; and 9) refusal to participate.

